### Study participants

A total of 390 patients with a history of an anterior ST-elevation MI (STEMI) treated successfully with PPCI 3–7 days earlier will be enrolled. Patients must be below 65 years old and must have severely impaired function of the left ventricle (LV), represented by an LVEF of < 40%. The participating hospitals will be the Al-Zahra Heart, Namazee, and Faghihi hospitals of Shiraz, Iran.

The inclusion criteria are as follows:Age (years): 18 to 65Either genderFirst MI in the preceding 3 to 7 daysPost-AMI LVEF < 40%Negative pregnancy test (for women of reproductive age)Written informed consent

The exclusion criteria are as follows:A history of any prior cardiac conditions (valvular, ischemic, or congenital disorders)Regional wall motion abnormalities outside the region of the infarctionLV dysfunction due to other etiologies like non-ischemic cardiomyopathy, anthracycline use, or ethanol abuse (> 6 oz./day regularly)Poor echocardiography windowActive infection, malignancy, or autoimmune disease

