### Intervention

This study will use cGMP-certified clinical-grade human WJ-MSCs (Cell Tech Pharmed Co. Ltd., Tehran, Iran). The cells will be transferred to the hospital on the same day as the infusion and are to be suspended in normal saline (0.9%). Each batch will be analyzed and certificated by a qualified individual, ensuring that the cells comply with the product specifications. Standard operational protocols will be followed during shipment and handling.

In the intervention group, all 130 patients will receive a single intracoronary infusion of 10^7^ WJ-MSCs alongside the conventional treatment that will be provided to the same number of patients in the control group. Patients in the intervention group will be taken to the cardiac catheterization lab, where the infusion of 10^7^ WJ-MSCs will be done through the intracoronary route. A bolus heparin dose (weight-based) is to be administered to patients with an activated clotting time below 200 seconds.

For catheterization, we will insert a therapeutic 6 Fr guiding catheter into the left coronary artery. Following the infusion of nitroglycerin (200 μg) through the catheter, we will assess the left anterior descending (LAD) artery and document the TIMI flow. A 0.014-inch soft-tipped guidewire wire will be inserted into the LAD at the distal edge of the stent. After passing through an over-the-wire balloon to the stented area, the balloon will be inflated until achieving occlusion. Following the removal of the guiding wire, we will connect an infusion syringe to the infusion catheter. WJ-MSCs will be infused at a rate of 2.5 ml/min and the total sample volume would be 7.5 cc. Low-pressure inflation (2–4 bar) will be performed to achieve occlusion with the balloon catheter, with complete coronary artery occlusion being ensured ahead of cell infusion through the use of dye. After the infusion of each third of the cells, we will pause the infusion, and TIMI coronary flow will be assessed with the contrast agent before the resumption of cell infusion. Once the cells are delivered across the three portions, we will place the coronary flow wire via the microinfusion catheter. No methods were used to increase adherence for this intervention as it was a one-off treatment with no need for continued adherence.

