The patients in both control and intervention groups will also receive standard Guideline directed medical therapy for acute myocardial infarction, consisting of Aspirin, ticagrelor, rosuvastatin, valsartan, and bisoprolol. Also based on the situation eplerenone and ICD insertion would be considered.

The original design of the study included a sham procedure for the control group but the local ethical committee refused that due to its invasive nature and obliged us to omit the sham procedure from the study protocol.

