### Follow-up and endpoints

Patients will receive daily visits from a cardiologist during hospitalization. The results of all physical examinations will be recorded, and patients will be monitored for early manifestations signaling arrhythmia, pulmonary embolism, or coronary artery injury. Blood tests will be done to measure fasting blood sugar, complete blood count, C-reactive protein, urea and electrolytes, liver function test, creatine kinase, and cardiac troponin T. An electrocardiogram (ECG) will also be obtained. Prior to the MSC infusion process, the cardiac evaluation will be completed using echocardiography. The initial EF will be established according to the wall motion score and Simpson’s rule. After the MSCs are delivered, once stable, a beta-blocker, angiotensin-converting enzyme (ACE) inhibitor, aldosterone antagonist, aspirin, ticagrelor, statin, and glyceryl trinitrate (spray or tablets) will be prescribed for the patient to use at home. A cardiac rehabilitation program will also be completed. Subsequent visits will be at ten days after discharge and then every three months when an ECG and blood tests will be requested. Echocardiography will be done during the six-month follow-up and the final visit, facilitating the evaluation of LV systolic function.

Our primary endpoint to assess the efficacy of the intervention will be the incidence of HF. Secondary endpoints include the improvement in LV function (through calculation of LVEF) after six months and after three years alongside echocardiographic changes in the left ventricular mass, left ventricular end-diastolic volume, left ventricular end-systolic diameter, and global longitudinal strain (measured via automated formulas in standard views) indices.

Data will be entered, encoded, became secure, and stored in a local database.

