### Adjudication of study measures

Before statistical analysis, adjudication of all measurements will be done by an experienced cardiology department member excluded from the research group. The adjudicator will assess the quality of each measurement and will exclude those with inadequate quality from the analysis, where they will be regarded as missing. An independent, blinded safety committee will evaluate potential major adverse cardiac events (MACEs). Once the adjudication process is complete, the finalized database will be unblinded.

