### Statistical analysis

Data will be kept anonymous until analysis, which is to be performed by an independent statistician external to the research group. Continuous variables will be summarized using the mean and standard deviation, while frequencies and percentages will be given for categorical data. The analysis will follow the intention-to-treat approach. Two-sided P-values will be used and a *P*<0.05 will be considered as significant.

The primary endpoint of the study which is the incidence of heart failure will be compared between groups using Cox regression analysis.

We will consider the EF to have improved significantly if a minimum increment of 3% is achieved after six months. The EF, as the secondary outcome, will be compared between the study groups using the independent t-test.

The baseline characteristics of the two study groups will also be compared using independent sample *T*-test.

Safety will be compared between the two groups according to the occurrence of MACEs (death, recurrent AMI, ICD insertion, non-target vessel revascularization, etc.) and serious adverse events (SAEs) using COX regression analysis. These events will be followed over time with Kaplan-Meier curves, which will allow us to understand their patterns.

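### The only revascularization named in the MACE list is in non-target vessels, although the procedure wires and balloon-occludes the recently stented LAD in the treated arm alone

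*Protocol article*

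**What the plan says.** The Statistical analysis section of the protocol article sets the safety comparison as "MACEs (death, recurrent AMI, ICD insertion, non-target vessel revascularization, etc.) and serious adverse events (SAEs) using COX regression analysis", with Kaplan-Meier curves to follow the events over time. Revascularization appears once in that list, at its open end ("ICD insertion, non-target vessel revascularization, etc"), and it is limited to non-target vessels.

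The Adjudication of study measures section gives these events their own review: "An independent, blinded safety committee will evaluate potential major adverse cardiac events (MACEs").

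Three other sections describe the procedure and who has it:

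- Study participants: patients with an "anterior ST-elevation MI (STEMI) treated successfully with PPCI 3–7 days earlier will be enrolled".
- Intervention, on the wire: "A 0.014-inch soft-tipped guidewire wire will be inserted into the LAD at the distal edge of the stent". On the balloon: "After passing through an over-the-wire balloon to the stented area, the balloon will be inflated until achieving occlusion".
- Intervention, on the control arm: the ethics committee "obliged us to omit the sham procedure from the study protocol".

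The Follow-up and endpoints section adds in-hospital surveillance, in which "patients will be monitored for early manifestations signaling arrhythmia, pulmonary embolism, or coronary artery injury". The Adverse events section lists complications of the intracoronary infusion among the issues the DSMB monitors, with quarterly reporting by study group.

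**The concern.** The procedure and the named revascularization component concern different vessels. The intervention works inside the LAD stent, while the component counts revascularization everywhere else. A patient who needs the LAD reopened after the infusion, without a new infarction, does not meet any printed MACE component. A patient who needs another artery treated does.

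This matters because exposure to the procedure differs completely between the arms. With no sham, the treated arm has a second coronary instrumentation and the control arm has none. The MACE comparison should therefore be able to detect harm in the instrumented vessel. The Ethical considerations section states that low inflation pressure and divided infusion will prevent infusion complications. The named MACE components test that statement only where a complication leads to death, infarction or ICD insertion.

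Blinded review is the second issue. Treating staff and patients know who was catheterized again, so blinded committee review of coronary events is valuable. The article assigns that committee MACEs only.

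**Working it through.** The article prints no target-vessel or MACE rate, so there is no figure to reproduce. The check sets the sections side by side.

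**Step 1: which vessel is the target vessel.** Entry requires an anterior STEMI treated by PPCI (Study participants). The wire goes to the distal edge of the LAD stent and the balloon is inflated in the stented area (Intervention). The article does not define target vessel. I take it to be the stented LAD, which is the ordinary reading.

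**Step 2: who is exposed.** The Intervention section gives 130 patients in the treated arm, all of whom have the infusion. Controls have no sham. The volume is 7.5 cc at 2.5 ml/min, so infusion time is 7.5 / 2.5 = 3 minutes in total, given in three portions.

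**Step 3: where each kind of event falls.**

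| Event | Named MACE component | Other stated route |
|---|---|---|
| LAD event causing death | Yes, death | SAE comparison; DSMB |
| LAD event causing recurrent infarction | Yes, recurrent AMI | SAE comparison if serious; DSMB |
| Repeat LAD revascularization without infarction or death | None | SAE comparison if serious; DSMB if classed as an infusion complication |
| LAD stent thrombosis without infarction or death | None | As above |
| Revascularization of another vessel | Yes | SAE comparison if serious |

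**Step 4: what the other routes provide.**

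- The SAE comparison uses the same Cox method and covers both arms. The article does not define an SAE. The endpoint also pools all serious events, so a signal specific to one vessel would be diluted.
- DSMB review of infusion complications is trial monitoring. Controls have no infusion, so that category cannot by itself give a comparison between arms.
- In-hospital monitoring for coronary injury is clinical surveillance. No analysis is attached to it.
- The blinded committee is assigned potential MACEs. The events in the third and fourth rows are not clearly among them. The Randomization and blinding section does keep outcome assessors unaware of allocation, so what is uncertain is review by the independent committee, not all blinding.

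**Result.** The gap is confined to the third and fourth rows: target-vessel events that stop short of infarction or death.

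**The case against.** The strongest reply is that the list ends in an open term, so target-vessel revascularization is unnamed but not excluded. A journal article may also leave the full component list to the protocol, analysis plan or committee charter, none of which is shown. That is fair, and asking only for a complete list would be asking for detail an article may omit. The point that stands is different. The article prints a specific qualifier on revascularization, and that qualifier points away from the instrumented vessel. An open term after a restricted item does not tell the reader that the restriction is lifted.

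Three stronger readings are tempting, and the document supports none of them.

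- A reader might infer that the composite counts no target-vessel event. It does count some: death and recurrent AMI carry no vessel restriction, so an LAD occlusion or thrombosis that causes either is included.
- A reader might infer that procedural harm is lost to the safety comparison, or that the comparison as a whole is biased towards showing no harm. The same sentence compares SAEs by arm, which would probably capture a serious LAD complication, and the DSMB monitors infusion complications.
- A reader might try to put a number on the missed events. That needs a procedural event rate, and the share of events that are neither infarction, death nor SAE. The article gives neither.

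Nor does the document show whether the qualifier is deliberate or a slip.

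**Conclusion.** The point holds in a limited form. The only named revascularization component covers vessels the procedure does not touch, while all 130 treated patients and no controls have the stented LAD wired and occluded. Repeat LAD revascularization or stent thrombosis without infarction or death falls in no named MACE component, and so is not clearly within the blinded committee's remit. The MACE comparison is less sensitive than it could be to the procedure's own risk, but serious harm has other routes into the safety assessment.

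The size in events cannot be given. The conclusion rests on two readings: that the target vessel is the stented LAD, and that the open end of the list does not already bring in target-vessel events. If a fuller document shows that it does, only the article's wording needs correcting. This is a cheap improvement to a stated component and does not affect the primary endpoint or the sample size.

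**What to change.** In the Statistical analysis section, replace the non-target-vessel component with any coronary revascularization (target and non-target vessel), and add stent thrombosis as a named component. In the Adjudication of study measures section, state that both go to the independent blinded safety committee. Report target-vessel events by arm on a separate line beside the composite, so that events in other vessels do not obscure them. If the present restriction is deliberate, give the reason.

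The cost is protocol and adjudication wording, slightly more committee work, and a check that the follow-up forms record which vessel was treated, since the article does not say that they do. The MACE result may look less favourable to the intervention. Treatment and sample size are unchanged.

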### Sample size

Since the primary outcome of this study is to compare the incidence of HF and considering the one-year incidence rate of 1.3% and 4% in the BAMI trial [3], it is predicted that in a 3-year period follow-up of considered for the present study, the incidence rate of this indicator will be 3.9% and 12% in intervention and control groups respectively. According to the formula $$\boldsymbol{n}=\frac{\frac{\mathbf{1}+\boldsymbol{R}}{\boldsymbol{R}}\overline{\ \boldsymbol{P}}\Big(\mathbf{1}-\overline{\boldsymbol{P}\Big)}{\left({\boldsymbol{t}}_{\boldsymbol{\alpha}, \boldsymbol{\nu}}+{\boldsymbol{t}}_{\boldsymbol{\beta} \left(\mathbf{1}\right),\boldsymbol{\nu}}\right)}^{\mathbf{2}}}{{\left(\boldsymbol{\partial}\right)}^{\mathbf{2}}}$$, and the enrolment ratio of 2:1 in case and control groups, and considering the first type error of 5% and the power of 80%, the required sample size is approximately 220 people in control and 118 people in case group***s***, which makes a total of 328 people. To increase the accuracy of sampling and the possibility of using regression models, the sample size was increased to 390 people. The sample size is approximate and the above formula is summarized. In the above formula $$\overline{P}$$, the weighted average of the values in the two groups is used, and the *t* values are equal to the 0.8 and 0.975 percentiles of the standard normal distribution and equal to 1.96 and 84. The denominator of the fraction (∂) is the difference of two amounts. R is the ratio of two groups, which is 2 here.

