### Adverse events

Adverse events will be reported by the study’s executive committee to an independent Data and Safety and Monitoring Board (DSMB). The DSMB will have the authority to stop the trial early if patient safety is compromised or if the primary research objective is met. If the presumed 5% statistically significant difference in EF was achieved, it would be considered as reaching the primary objective of the study. A stringent statistical threshold would be used as the stopping rule. All safety issues (unanticipated SAEs, mortality, intracoronary infusion complications, severe arrhythmias, etc.) will be monitored by the DSMB, and the DSMB statistician will report the occurrence of safety issues in each study group quarterly. All deaths will be reported. Auditing would be done by DSMB on a 6-month interval and is independent of investigators.

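### The one stated between-arm test of SAEs is a Cox comparison with no early window, which dilutes procedural harm that only the intervention arm can have; add a day-30 comparison

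*Protocol article*

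**What the plan says.** All references are to the protocol article.

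- **Statistical analysis.** Safety is compared between the groups on MACEs and "serious adverse events (SAEs) using COX regression analysis". Kaplan-Meier curves follow the events over time so that their pattern can be seen. No time window is given. SAE is not defined, and HF events are neither included in the SAEs nor excluded. The named MACE components do not include HF, but the list is left open.
- **Intervention.** Infused patients have a balloon occlusion of the stented LAD and an infusion in three portions. The ethics committee had the sham procedure removed, so controls have no procedure.
- **Follow-up and endpoints.** During the hospital stay, "patients will be monitored for early manifestations signaling arrhythmia, pulmonary embolism, or coronary artery injury". The primary endpoint is the incidence of HF; it is not defined as hospitalisation.
- **Adverse events.** The DSMB monitors "unanticipated SAEs, mortality, intracoronary infusion complications, severe arrhythmias, etc", and its statistician reports these by study group each quarter.
- **Sample size.** The assumption for 3 years is that "the incidence rate of this indicator will be 3.9% and 12% in intervention and control groups respectively".

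**The concern.** The harm specific to this intervention is early and can occur in one arm only. The stated test sums SAEs over years in which both arms collect unrelated events. A short excess at the start then becomes a small part of a long comparison, and its hazard ratio is pulled toward 1. The Kaplan-Meier curves would display an early step, but no early estimate or interval is planned with them.

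There is a second, conditional problem. If HF admissions are entered as SAEs, the benefit the trial hopes for also lowers the SAE count in the intervention arm and works against any procedural excess.

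At stake is the balance the trial must report: the risk of another coronary procedure within days of an infarction against less HF over 3 years. The stated test gives little information on the first half of that balance.

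**Working it through.** **The plan's own figures.** The article gives no power or sample size for safety, so there is none to reproduce. The HF rates do reproduce: 3 × 1.3% = 3.9% and 3 × 4% = 12%. The total is 390 with 130 infused, so 260 controls by subtraction. This fits the Sample size section, where control is the larger arm ("the required sample size is approximately 220 people in control and 118 people in case"). The Intervention section's remark that the control arm has the same number of patients does not fit, and 260 is used here. Tests are two-sided at 5%.

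**Assumptions not in the article.** Other SAEs affect 20% over 3 years at a constant rate, equal in both arms. The procedural excess is 5% of infused patients, within 7 days. Follow-up is 2 to 3 years, because Trial status ends recruitment in Nov 2022 and data collection in Nov 2024. Both arms may have extra background SAEs in the first 30 days, varied from 0 to 6%.

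**1. Dilution, with no HF event counted as an SAE**

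Risk of any SAE at 3 years:
- control: 20%
- intervention: 1 − 0.80 × 0.95 = 24.0%
- approximate hazard ratio: ln(0.76)/ln(0.80) = 0.274/0.223 = 1.23

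Risk at day 30, with no extra early background:
- control: 1 − 0.80^(30/1095.75) = 0.6%
- intervention: 1 − 0.994 × 0.95 = 5.6%

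The same harm is 4 points on a base of 20% in one analysis and 5 points on a base under 1% in the other.

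The chance of detecting harm was simulated with the log-rank statistic, Z = (O − E)/√V, which is the Cox score test. Two sets of simulated trials gave about 18 to 23% and about 16 to 20%. Exact power of Fisher's test at day 30 (130 vs 260):

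| Extra background SAEs in first 30 days | Day-30 risk, control vs intervention | Chance of detecting the 5% excess |
|---|---|---|
| 0% | 0.6% vs 5.6% | 85% |
| 2% | 2.6% vs 7.5% | 56% |
| 4% | 4.6% vs 9.4% | 42% |
| 6% | 6.6% vs 11.2% | 33% |

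**2. Offset, only if HF events are SAEs**

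The infusion SAE rate h that makes the two arms' 3-year SAE risks equal solves (1 − 0.039)(1 − h) = 1 − 0.12:
- all HF events are SAEs: h = 1 − 0.88/0.961 = 8.4%, and 0.084 × 130 ≈ 11 patients
- half are SAEs: h = 1 − 0.94/0.9805 = 4.1%
- all are SAEs, with the 2-year hospitalisation rates the article cites from the earlier bone marrow cell trial (2.7% vs 8.1%): h = 1 − 0.919/0.973 = 5.5%

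With all HF events counted and a 5% excess, the 3-year risks are 1 − 0.80 × 0.88 = 29.6% in control and 1 − 0.80 × 0.961 × 0.95 = 27.0% in the intervention arm. The direction reverses, and the log-rank test detects harm in about 2% of trials. The day-30 test still detects it in 29 to 75% over the same range of early background.

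**The case against.** The strongest case against has four parts.

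- **Left to other documents.** The SAE definition, safety windows and tabulation by period usually stand in the full protocol or SAP, and their absence from an article is no fault. This stands for the definition, and no point is made of it. It does not fully answer the dilution, because the article does state the between-arm safety test and that test suits early one-arm harm poorly.
- **Early harm is watched elsewhere.** The DSMB sees infusion complications by arm, a blinded committee evaluates MACEs, and the curves would show a first-week step. This stands. But monitoring protects patients during the trial; it does not supply the estimate with an interval that readers need at the end.
- **The day-30 advantage depends on the model.** These patients are 3 to 7 days past an anterior infarction with LVEF below 40%, so early background SAEs are plausible. At a 10% background, day-30 power for a 5% excess falls to about 23%. This stands, and is why a range is given.
- **Dropping HF events has a price.** It could hide HF caused by the infusion, and an all-SAE comparison of randomised groups is a legitimate measure of net harm. This stands, so exclusion is suitable only as a sensitivity analysis.

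A reader might infer more: that the SAE comparison counts HF hospitalisations and so would make the procedure look safe. The article does not support this. SAE is undefined, the primary endpoint is HF incidence rather than admission, the named MACE items omit HF, and the DSMB reports and the curves would both bring out an early excess.

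**Conclusion.** The point holds, and rests mainly on dilution, which needs no assumption about HF events. For a 5% first-week excess, the stated Cox comparison would detect harm in about one trial in five, against about 33 to 85% for a day-30 comparison. These figures depend on the assumed 5% excess, the 20% other-SAE rate and the early background of 0 to 6%, none of which the article gives. At higher early background rates the gain in power narrows. The safety comparison is also read here as covering all follow-up, because no window is stated.

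The offset is conditional. It is at most about 8.4% (11 of 130) if every HF event is an SAE and the planning rates come true, and smaller if only some are. This is a worthwhile, low-cost improvement to the safety analysis. It does not show that the planned analyses are invalid.

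**What to change.** In the Statistical analysis section:

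1. Keep the planned Cox and Kaplan-Meier analyses of MACEs and SAEs.
2. Add, as the main peri-procedural safety result, a comparison by randomised group of SAEs and deaths from randomisation to day 30, given as a risk difference with 95% confidence interval.
3. Report the proportion of catheterised patients with an infusion complication, with an exact confidence interval.
4. State whether HF events count as SAEs. Report the long-term SAE comparison with and without primary-endpoint HF events, the version without them as a sensitivity analysis.

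This changes analysis wording only and uses events the trial already monitors; no visits or patients are added. The cost is a few more tables and wide intervals from small early counts: a 5% excess is only 6 or 7 of 130 infused patients.
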